## Abstract

**Background:**

While psychological interventions are effective at improving symptoms of psychosis, accessible, cost- and time-efficient treatments remain limited. Personalized medicine has emerged as a promising approach, tailoring interventions to individual needs. Metacognitive Training (MCT), with its established efficacy and adaptable format, is well-suited for personalization. The PERMEPSY project (Towards a Personalized Medicine Approach to Psychological Treatment for Psychosis) aims to deliver tailored MCT intervention for individuals with psychosis.

**Methods:**

PERMEPSY is an international study funded by ERAPerMed (JTC2022) involving five clinical partners (Spain, Chile, France, Germany, Poland) and one technological partner (Spain). The project involves a proof-of-concept clinical trial recruiting 51 participants from each center for a total of 255 adult participants with psychosis in a prospective study (Registration: NCT06603922, 19-09-2024). The trial will test the efficacy of a Machine Learning (ML)-derived platform at predicting clinical and functional outcomes from baseline scores and compare a personalized MCT (P-MCT) to a classical MCT based on the platform’s predictions.

**Aims:**

PERMEPSY seeks to (1) develop and test the predictive power of an algorithm that could support decision-making, and (2) ascertain whether P-MCT is more effective than MCT at improving key symptoms and cognitive impairments associated to psychosis.

**Results:**

A harmonized retrospective database enabled the development of a predictive ML algorithm, integrated into an innovative platform. This platform provides clinicians with the information needed to deliver P-MCT. Predictions include changes in positive symptoms (e.g., delusions), insight, self-esteem, and treatment adherence.

**Discussion:**

By integrating diverse data types and innovative technology, PERMEPSY addresses the need for personalized, effective treatment in psychosis, aiming to reduce individual and systemic burdens while supporting clinicians in their decision-making.

## Introduction

1

Schizophrenia and other psychotic disorders are severe mental health disorders affecting approximately 2% of the global population (1), with a 12-month prevalence of 4.03 per 1000 persons (2) and an incidence of all psychotic disorders of 26.6 per 100.000 person-years (3), leading to significant levels of disability and generating a considerable burden for patients, caregivers, and healthcare systems. In Europe, the average annual direct cost per patient is estimated at 5.800€ (4).

Although pharmacological treatment with antipsychotics is widely used, it does not always improve functional outcomes, with discontinuation rates ranging from 50% to 75% among patients (5). In this context, psychological interventions have demonstrated to be beneficial, even in the absence of pharmacological treatment, with 40% of patients experiencing significant symptom improvement as a result of psychological interventions (6).

Metacognitive Training (MCT) is a low-threshold, manualized intervention available free of charge in 40 languages (available www.uke.de/mct). Based on the principles of Cognitive Behavioral Therapy (CBT), MCT is an effective psychological intervention for psychosis that has been incorporated into the latest World Health Organization (WHO) treatment guidelines (7), and is recommended by the German Psychiatric Association (DGPPN) (8), the German Psychological Society (DGP) (9), and the Australian and New Zealand College of Psychiatrists (10).Recent quantitative syntheses have provided a detailed picture of the specific clinical targets most responsive to MCT in schizophrenia. A comprehensive meta-review (11) reported medium to large effects on delusions (*g* = 0.64), positive symptoms (*g* = 0.47), and total psychotic symptoms (*g* = 0.39), with smaller but significant effects on hallucinations (*g* = 0.27) and negative symptoms (*g* = 0.23). Additional meta-analyses have shown improvements in general functioning (*g* = 0.41), self-esteem (*g* = 0.17), and cognitive biases (*g* = 0.16) (12), as well as global social cognition (*d* = 0.28) and theory of mind (*d* = 0.27) (13). MCT also improves insight (*g* = 0.35), although no significant effects have been found for global neurocognition (14), aligning with the intervention’s theoretical focus on metacognitive processes rather than fundamental cognitive capacities. These findings are consistent with a recent graded evidence review (15), which assigned a WFSBP-1 level of evidence to MCT for reducing positive symptoms, delusions, and total psychotic symptoms; and WFSBP-3 for hallucinations, negative symptoms, general functioning, theory of mind, jumping to conclusions, and insight. Together, this literature provides a detailed and clinically relevant framework of expected treatment targets. However, despite its effectiveness, there are currently no predictive models capable of assessing whether an individual is likely to respond well to MCT or which MCT modules would be most suitable for improving a patient’s prognosis.

Multiple studies (16–18) have identified cognitive biases, symptom severity, self-esteem, age of onset, and sex as key moderators of treatment efficacy. Similarly, gender differences in response to MCT have been established, with another study finding that women with psychosis respond differently and more favorably to MCT than men (19, 20).

Biomarkers are considered essential for identifying patient subgroups and enabling personalized approaches in precision medicine in psychiatry (21, 22). Considering biological variables, potential inflammatory biomarkers associated with MCT response include C-reactive protein, extensively studied in schizophrenia due to its correlation with symptom severity, and leukocyte counts, which are linked to grey matter volume (23, 24). Previous studies support the role of SP1 and SP4 transcription factors as biomarkers that may be modulated by MCT treatment (25–27). Therefore, considering the previous literature biomarkers may become an important moderator to consider in the treatment of psychosis, and enable subgroup analyses that could help determine biological profiles of treatment response.

The extensive research and quality of studies researching the effect of MCT provides an ideal context for developing a data-driven approach using an analytical pipeline based on machine learning (ML) based predictive models. Predictive models are used both for diagnosis and prognosis in the personalization of psychiatric healthcare (28, 29), and ML serves as a natural enabler of personalized medicine (30–32) when combined with knowledge extraction and explainability strategies (33).

Most researchers and clinicians agree that the treatment of psychotic patients should be personalized and tailored to their specific needs (34). However, its implementation in clinical practice remains limited and depends on overcoming several challenges One reason is the economic cost of personalization and its adoption by clinicians (35) among others. Another significant barrier is the limited scientific knowledge regarding the factors that should guide treatment customization, an ongoing challenge in mental health research (36).

The PERMEPSY Project emerges as a response to this need and available data, with the aim of developing a predictive prototype platform to assist clinicians in determining the optimal psychological MCT treatment strategy for each individual. Predictions are based on each individual’s personal characteristics and baseline scores in various clinical, cognitive and functional outcomes. These outcomes were selected both by data-driven insights derived from the ML analysis and an extensive review of the literature by consortium partners (11, 15, 19, 37, 38), which took place prior to the development of the prototype platform (39) to identify key indicators of treatment efficacy in psychosis. This innovative approach leverages ML techniques to analyze a broad spectrum of variables, from environmental factors to biomarkers, thus reflecting the multifactorial nature of mental illnesses.

The technological solutions employed in PERMEPSY, such as ML, can facilitate the identification of key variables in predicting treatment response. This may help clinicians focus on both objective and subjective problematic areas, consider the course of illness, and adopt a gender-sensitive approach early on in the treatment stage. The project also integrates methodological advancements, ensuring the personalized treatment for each patient is data-driven and supported by the prototype platform.

The overarching goal is to develop an open platform that supports clinicians in treatment decision-making, enabling them to predict MCT response, recommend personalized MCT (P-MCT) treatment, and provide evidence-based information. This will assist clinicians in making informed decisions regarding psychological interventions for psychosis. A clinical trial will be conducted to validate both the platform and the predictive model for personalized MCT.

Therefore, the primary objective of this prospective clinical trial is (1) to evaluate the efficacy of P-MCT compared to classical MCT in individuals diagnosed with psychosis, focusing on improvements in positive symptoms (especially delusions), insight, self-esteem, and treatment adherence. Moreover, some specific objectives of this trial include: (2) to validate the ML-based predictive model’s capacity to anticipate MCT treatment response, (3) to evaluate patient satisfaction with P-MCT comparing to classical MCT, integrating both quantitative measures and qualitative insights from focus groups, and (4) to refine the platform’s predictive algorithm through integration of treatment outcome data.

Given that P-MCT has not been previously evaluated and that the ML platform is a novel tool, hypotheses 2–4 are considered exploratory. Our hypotheses are as follows:

H1 - Primary (Comparative efficacy): P-MCT will yield comparable or superior improvements than classical MCT in outcome variables measuring treatment efficacy (positive symptoms, insight, self-esteem, and treatment adherence).H2 - Exploratory (Platform validation): The ML-based predictive model will demonstrate significant predictive capacity to anticipate post-treatment response to MCT on positive symptoms (especially delusions), insight, self-esteem, and treatment adherence, as assessed by the AUC (Area Under the Curve).H3 - Exploratory (Patient satisfaction): Patient satisfaction with P-MCT will be comparable or greater than with classical MCT, as assessed through both quantitative measures and qualitative insights from focus groups.H4 - Exploratory (Platform improvement): The integration of multimodal comprehensive pre-post treatment data from the classical MCT group will refine the machine learning algorithm, resulting in improved predictive accuracy for future patient cohorts.

## Methods and analysis

2

### Participants

2.2

The sample will consist of patients with a diagnosis of non-affective psychosis, according to DSM-5 criteria (40). Participants will be recruited from multiple clinical centers (associated to the following clinical partners: Fundació Sant Joan de Déu [FSJD], Universitätsklinikum Hamburg-Eppendorf [UKE], Hôpitaux Universitaires de Strasbourg [UHS], Centre Hospitalier Universitaire de Nice (CHU de Nice), Institute of Psychology, Polish Academy of Science [PAoS] and Universidad del Valparaíso [UV]), including both inpatient and outpatient services, with a minimum of 51 patients per center. Recruitment will occur in psychiatric hospitals and community mental health centers. To facilitate recruitment, clinicians at these sites will receive detailed information about the study’s inclusion and exclusion criteria through local meetings and internal communications. Additionally, announcements will be posted in the centers to raise awareness and encourage referrals during routine clinical care. Inclusion criteria are (1): A DSM-5 diagnosis of non-affective psychosis (2); presence of positive symptoms during the past year (represented by a Positive and Negative Syndrome Scale [PANSS (41)] score equal or over 3 on the items measuring Delusions, Suspiciousness, or Grandiosity); (3) aged between 18 and 65 years old; (4) stable clinical condition with no expected changes in medication (as confirmed by clinical services); (5) no severe cognitive deficits (global assessment and/or information from clinical services). Exclusion criteria are: (1) previous attendance in MCT groups within the past year; (2) neurological disorders, history of head trauma, or premorbid IQ below 70 (based on medical reports and/or other sources); (3) a score equal or over 6 on the Hostility and Suspiciousness items of the PANSS Positive subscale; (4) aggressive behavior (reported by clinical services); (5) high suicide risk (verified through the DIAMOND clinical interview). Patients who do not meet the inclusion criteria will not be enrolled in the study but will be offered alternative treatment options or MCT at later stages.

The inclusion and exclusion criteria were designed to balance internal validity with real-world clinical representativeness. Criteria were primarily informed by those most employed across the studies that contributed to the development of the ML predictive platform, ensuring consistency between the training dataset and prospective trial population. The requirement for positive symptoms (PANSS ≥ 3) ensures the presence of clinically relevant MCT targets, while the upper threshold for hostility/suspiciousness (PANSS ≤ 6) maintains therapeutic dynamics and avoid group issues, while maintaining group representativeness and excluding severe cases and at the same time without overly restricting sample representativeness. The stable medication criterion reduces confounding from pharmacological changes, while cognitive and safety exclusions (IQ < 70, high suicide risk, aggressive behavior) ensure participants can meaningfully engage with the intervention. This approach avoids overly stringent criteria that would limit generalizability while maintaining sufficient homogeneity to detect treatment effects (42).

### Measures

2.3

Data will be collected on sociodemographic, clinical, cognitive (neurocognitive, metacognitive, social-cognitive), and psychological variables. Given the transnational nature of the study, official validated translations of all instruments were used for each participating country. When validated translations existed but item ordering differed between countries, administration was standardized according to the official English version to ensure consistency across sites. For instruments lacking official translations in some specific languages (e.g., The Internal, Personal, and Situational Attributions Questionnaire (IPSAQ), Fish Task) and for consortium-developed scales (e.g., modified Patient-Reported Impact of Symptoms in Schizophrenia (PRISS) scale to monitor symptoms during treatment, satisfaction with MCT treatment), forward-backward translation procedures were conducted by independent bilingual researchers to ensure semantic and conceptual equivalence. The instruments used and their characteristics are presented in **Supplementary Table S1**.

Blood samples will be drawn from participants at baseline and post-treatment. In both centers collecting blood samples (FSJD and UV), leukocyte subpopulation counts obtained from blood count analyses and C-reactive protein levels will be collected. At the FSJD site, peripheral expression levels of SP transcription factors (SP1 and SP4) will be analyzed as part of a subproject aimed at identifying biomarkers with transcriptional reprogramming capacity involved in the response to MCT. Biomarkers are included because they provide objective biological indicators of inflammatory and transcriptional processes that may influence cognitive functioning and symptom severity in psychosis. These processes are increasingly recognized as moderators of treatment response in psychological interventions. Including biomarkers enables subgroup analyses to determine whether MCT efficacy varies by biological profile.

Incorporating biomarker data will refine the ML algorithm. This iterative process will determine which biomarkers consistently improve predictive accuracy, guiding future versions of the platform toward more biologically informed personalization.

Following the intervention, qualitative data on patient satisfaction will be collected through focus groups at each center, exploring participants’ experiences, perceived benefits, barriers, and overall satisfaction with the intervention. This data will complement the quantitative measures collected post-treatment and at follow-up.

### Data collection

2.4

Pre-treatment, post-treatment, and follow-up assessments will be conducted by blinded, trained psychologists at each site. These evaluations will take place over the course of one to two interviews. Assessors will be trained in standardized administration of instruments to ensure equal collection across centers.

Nursing staff will be responsible for performing cubital vein blood counts for separation of peripheral blood mononuclear cells. Blood will be stored at 4°C until processed. Additionally, the transfer of samples to the Parc Sanitari Sant Joan de Déu (PSSJD) biobank will be requested following a prior agreement for participation in the study. The analyses will be conducted at the PSSJD Molecular Psychiatry Laboratory (SP1 and SP4 analysis) and the Hospital Sant Joan de Déu Clinical Laboratory (C-reactive protein and complete blood count). Blood will be collected from participants in the sites at UV and FSJD.

This study is in accordance with the World Medical Association’s Declaration of Helsinki and was approved by the Sant Joan de Déu Ethics Committee (Reference: PIC-110-24), the Institute of Psychology, Polish Academy of Science (Reference: IP.403.21.2024), Ethics Committee of Valparaíso San Antonio Health Service of Chile (Reference: N°48/2024), the local psychological ethics committee at the center for psychosocial medicine (LPEK) at the University Medical Center Hamburg-Eppendorf (Reference: LPEK-0796) and the Comité de protection des personnes Ile de France (Reference: 25.02907.000469). Since the study involves human participants, evaluations will be conducted once informed consent has been obtained. The personnel conducting the assessments, blood extractions, blood counts, and molecular analyses will be blind to the study condition assigned to each participant. All variables will be measured at baseline, post-treatment, and six months after completion, except for the DIAMOND and TEC scales, which will only be administered at baseline; the PRISS scale, which will be administered at the end of each session to monitor symptoms during treatment; patient satisfaction with treatment, which will be collected post-treatment and at follow-up; and the biological samples, which will be collected only within two weeks before the start of the intervention and within two weeks after its completion.

Data will be entered into a secure, password-protected database. Coding will follow standardized formats. Range checks and validation rules will be applied. Data will be stored at each site in compliance with GDPR and local regulations.

For qualitative data, each center will carry out two focus groups (one for the personalized MCT group and one for the classical MCT group), with 5–10 participants per group. Sessions will be audio-recorded, transcribed verbatim, anonymized, and translated into English. Field notes will also be kept. Monthly meetings with representatives from all centers will be held to triangulate results and ensure consistency across sites.

### Interventions

2.5

Participants who meet inclusion criteria will be randomized into one of the two study conditions: (1) Metacognitive Training (MCT) and (2) Personalized Metacognitive Training (P-MCT). Sessions will run concurrently in all centers from October 2024 until April 2025.

MCT consists of 10 one-hour group sessions (3–10 participants). It includes ten modules referring to common cognitive issues and biases in solving problems in psychosis. MCT is effective in reducing symptoms and improving cognitive biases that are involved in the onset and maintenance of psychosis (12). The topics of MCT are the following: attribution blaming and taking credit (module 1), jumping to conclusions (modules 2 & 7), changing beliefs (module 3), deficits in theory of mind and other social cognition domains (modules 4 and 6), overconfidence in errors (module 5), mood (module 8), self-esteem (module 9) and self-stigma (module 10). Each session follows a protocol defined in the manual ‘Metacognitive Training for Psychosis’ (MCT). The format (online or in-person) and frequency (once or twice a week) will vary by center depending on staff resources; this information will be considered as covariables in the analysis. Participants receive worksheets at the end of each module to continue working on the modules at home.

The personalization strategy was developed through a two-day in-person consortium meeting dedicated to integrating ML predictions into treatment. Consistent with the dual objectives of personalizing treatment while maintaining accessibility, the consortium decided against full individualization of sessions, which would have reduced the number of patients able to access group-based MCT. Instead, P-MCT differs from classical MCT exclusively in homework content, while group sessions remained identical in both groups. Participants are asked to discuss their homework tasks with their MCT therapist exclusively to preserve blindness to treatment condition. After the follow-up assessment, participants are informed of which treatment group they were allocated to and the homework tasks given to the other group, as well as any extra personalized tasks not received are offered to them.

A key strategic decision concerned how to personalize homework. Rather than reinforcing domains predicted to improve most, the consortium adopted a recovery-oriented approach by targeting the three outcome domains with the lowest predicted improvement out of the five domains discussed to best represent successful treatment response (positive symptoms, insight, self-esteem, and treatment adherence). personalized exercises were developed by clinicians within the consortium using (1) clinical practice guidelines and (2) predictive features identified using SHAP values from the ML model (39), ensuring alignment between clinical relevance and data-driven indicators. Sixteen exercises (four per outcome domain) were developed and standardized in length and complexity to ensure that any differences in treatment effects arise from personalization rather than workload. Homework assignment follows a fixed and reproducible rule: for each participant, the platform identifies the three outcome domains with the lowest predicted improvement. Across the ten MCT sessions, homework is assigned by cycling repeatedly through these three domains (Domain 1 → Domain 2 → Domain 3 → repeat). Because the program includes ten sessions, Domain 1 receives four exercises, while Domains 2 and 3 each receive three exercises. Within each domain, exercises are delivered sequentially (Exercise 1 to Exercise 4), ensuring a consistent rotation structure tailored to the participant’s predicted needs while maintaining standardization of the overall intervention. The established order of tasks represents the degree of relevance of the related factor detected by the ML model. For instance, in the Positive Symptom analysis, related factors associated with improvement in positive symptoms included positive symptoms themselves, negative symptoms, JTC and self-reflection, in this order. As a result, in order to target positive symptoms, the four homework tasks related to this domain include (1) psychoeducation on positive symptoms, (2) an activity planner to reduce negative symptoms, (3) a task to identify and correct JTC biases, combining self-reflection with JTC improvement, and (4) positive symptoms psychoeducation on stress management.

Group sessions will be delivered by trained clinical psychologists or psychiatrists (https://clinical-neuropsychology.de/metacognitive-training-e-training/) with prior experience in MCT. All facilitators will undergo standardized training in both P-MCT and classical MCT, and monthly meetings will include supervision to ensure protocol fidelity. Data from all participants’ baseline assessment will be input into the platform, and its results will be used to personalize the homework for participants in the P-MCT condition only. Results from the MCT condition will be stored and only used to confirm the platform’s prediction accuracy.

In terms of adherence monitoring and ensuring protocol fidelity, participants are asked to complete a questionnaire after every session attended to record their symptomatology over the previous seven days, the completion of homework and their attendance to the session (session number and module attended). Other than the offered MCT sessions, participants will continue to receive their routine care through their usual center, including medication and any other non-MCT psychological treatment. Clinicians and MCT trainers will monitor for adverse events and discontinue the allocated intervention in case of worsening symptoms. Participants are allowed to drop out of the study at any point, and they are informed that they have the right to withdraw from their therapy group at any time when they sign the informed consent forms. Reasons for withdrawal, adherence to sessions and homework and reasons for missing data will be recorded.

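### Matching exercise length and complexity cannot make personalization the cause of a P-MCT advantage, because new homework content and platform-based selection always come together

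*Protocol article*

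**What the plan says.** All of the following is in section 2.5 (Interventions) of the protocol article unless noted.

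- **Difference between arms:** "P-MCT differs from classical MCT exclusively in homework content, while group sessions remained identical in both groups". There are two arms only.
- **Classical MCT homework:** "Participants receive worksheets at the end of each module to continue working on the modules at home".
- **P-MCT homework:** "Sixteen exercises (four per outcome domain) were developed and standardized in length and complexity". On their origin: "personalized exercises were developed by clinicians within the consortium using (1) clinical practice guidelines and (2) predictive features identified using SHAP values".
- **Selection rule:** for each participant "the platform identifies the three outcome domains with the lowest predicted improvement", and homework rotates through these three. "Because the program includes ten sessions, Domain 1 receives four exercises, while Domains 2 and 3 each receive three exercises".
- **Attribution:** the exercises were "standardized in length and complexity to ensure that any differences in treatment effects arise from personalization rather than workload".

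The Introduction gives the H1 outcomes as positive symptoms, insight, self-esteem and treatment adherence. These are the four domains for which the exercises were written.

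**The concern.** The attribution sentence treats workload as the only rival to personalization. A second rival is left in place. The P-MCT arm gets different homework material, written with the H1 outcomes in view, and it also gets a platform-driven choice among that material. Material aimed at the endpoints could outperform the module worksheets even if the platform's ranking of domains carried no information.

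What is at stake is the meaning of a positive H1. The Introduction says that the trial is to validate both the platform and the predictive model for personalized MCT, and the Discussion mentions preparation for medical-device certification. Taken together with the sentence in section 2.5, a positive H1 invites the conclusion that ML-guided selection improves outcome. The two-arm contrast cannot show that.

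**Working it through.** **1. What each arm receives**

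| Component | Classical MCT | P-MCT |
|---|---|---|
| Group sessions | identical | identical |
| Homework material | module worksheets | exercises from the new pool of 16 |
| Material written around the H1 domains | not stated for the worksheets | yes, four exercises per domain |
| Platform-based selection | no | yes |

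The homework material and the selection change together between the columns. To separate them, some participants would have to receive the new exercises in a fixed, random or otherwise non-platform selection. No arm does.

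**2. What standardization can remove**

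Equal length and complexity makes workload an unlikely explanation, provided that the exercises were matched to the control worksheets. The article does not say whether they were matched to the worksheets or only to one another. In either case, matching does not touch the difference in content.

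**3. Whether a planned analysis separates the two**

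- Section 2.7.1 compares the arms as randomized, so it estimates the combined effect.
- Section 2.7.2 compares P-MCT outcomes with baseline predictions. Those participants had both the new content and the selection, so the confounding is the same.
- Section 2.7.2 also tests prediction accuracy in the classical MCT group (AUC, RMSE, R²). This bears on whether the predictions behind the ranking are accurate. It does not test whether giving homework in the domains predicted to improve least is beneficial.

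**4. Illustration: how much the selection varies the homework**

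Assumptions: four domains, the stated rotation, and exercises that replace the worksheets.

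The plan's own figures reproduce. The pool is 4 domains × 4 exercises = 16. Over ten sessions, Domain 1 is used in sessions 1, 4, 7 and 10, Domain 2 in sessions 2, 5 and 8, and Domain 3 in sessions 3, 6 and 9. That gives 4 + 3 + 3 = 10.

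The number of ordered choices of three domains from four is 4 × 3 × 2 = 24, which makes 24 × 23 / 2 = 276 pairs of different orders. Every participant gets Exercises 1 to 3 in each of three domains, plus Exercise 4 in Domain 1. For two participants with different orders:

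| Domains in common | Same Domain 1? | Exercises shared | Pairs |
|---|---|---|---|
| 3 | yes | 9 + 1 = 10 | 12 |
| 3 | no | 9 | 48 |
| 2 | yes | 6 + 1 = 7 | 48 |
| 2 | no | 6 | 168 |

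Check: 12 + 48 + 48 + 168 = 276. The platform's ranking therefore changes at most 10 − 6 = 4 of the 10 exercises between two P-MCT participants. The order of delivery is ignored in this count.

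**5. Sensitivity to the number of domains**

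Section 2.5 also speaks of five domains, although it lists four. With five, two choices of three domains overlap in at least 3 + 3 − 5 = 1 domain, so the minimum shared would fall to 3 exercises. Five domains at four exercises each would need 20 exercises, and the article gives 16, so four is the reading that fits.

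**The case against.** **The sentence excludes workload only.** Its closing words limit it, and it explains why the exercises were standardized. This is partly fair, since it is one subordinate clause. The clause nevertheless names personalization as the source of any difference, and that is more than excluding workload.

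**Personalization means the whole homework strategy.** Section 2.5 calls the new tasks personalized exercises, and their content and order draw on SHAP features of the ML model, so content is partly model-driven at group level. This stands, and it blurs a clean split between content and selection. It also means that the contrast is a package, which the text should then say.

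**The package is already visible.** H1 compares P-MCT with classical MCT and does not say that a positive result proves the ranking works. Section 2.5 discloses that only homework differs. This also stands, and it lowers the severity. The attribution sentence still contradicts what the careful reader can work out.

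**Stronger readings that the document does not support:**

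- A reader might infer that P-MCT replaces all ten worksheets, so that homework differs in 10 of 10 tasks. Replacement is plausible: the arms differ only in homework content, the sentence implies matched workload, and the other group's tasks are offered only after follow-up. The article never states it, and the worksheets are not shown. Some themes overlap: jumping to conclusions appears in a P-MCT exercise and in modules 2 and 7, and self-esteem is both a P-MCT domain and module 9. If the exercises were added to the worksheets instead, workload would differ too and the sentence would fail more plainly.
- A reader might take the task counts to show that new content is the larger part of the treatment contrast. Counts of shared exercises do not measure shares of effect.
- A reader might say that a null result would reveal nothing about the ranking. H2 gives separate evidence on the accuracy of the predictions, so that is too absolute.

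**Conclusion.** The attribution in section 2.5 describes a property that the design does not have. New outcome-targeted exercises and platform-based selection are fully confounded in a two-arm trial, and neither section 2.7.1 nor section 2.7.2 separates them. This conclusion follows from the description of the arms. It needs neither the four-domain count nor the assumption that the worksheets are replaced.

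The range of 6 to 10 shared exercises is an illustration that rests on both of those assumptions. It shows only that most of a P-MCT participant's exercises would be the same under a different ranking.

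The randomized comparison of P-MCT with classical MCT stays valid as a comparison of packages in a trial that section 2.1 calls exploratory and proof-of-concept. The point is therefore a should-fix, concerning what H1 may be said to show.

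**What to change.** 1. In section 2.5, limit the sentence to workload: the exercises were standardized so that differences between arms do not arise from workload. Delete the attribution to personalization.
2. In H1 and section 2.5, state that the trial compares a homework package, namely new domain-targeted exercises plus platform-based assignment, with the classical MCT worksheets.
3. State that H1 will be reported as the effect of that package, and not as evidence that ML-guided selection itself improves outcome.

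This is a change of wording. Arms, randomization, sample size, endpoints and analyses are unaffected. The downside is a narrower headline claim. Isolating the selection would take a comparison group given the same exercise pool without platform-based selection. That is a different design and is not asked for here.
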